### Information collection

2.8

#### Demographic data

2.8.1

Including the patient's gender, age, nationality, occupation, height, weight, and body mass index.

#### TCM syndrome types of CHD angina pectoris

2.8.2

The TCM syndrome type is derived from the diagnosis of the existing cases. If there is no syndrome diagnosis, the 2 trained physicians with more than 5 years of practicing qualifications will judge each other. If there is any dispute, they will be submitted to the superior doctor for final review.

#### Western medicine typing of CHD angina pectoris

2.8.3

Western medicine classification of CHD angina is derived from the diagnosis of existing cases. If there is no classification diagnosis, 2 of the trained physicians with more than 5 years of practicing qualifications judge each other. If there is any dispute, they will be submitted to the superior doctor for final review.

#### Evaluation criteria for clinical efficacy of CHD angina pectoris

2.8.4

1.Main events: The incidence of cardiovascular events includes acute myocardial infarction, PCI or CABG.2.Secondary events(a)All causes of death.(b)Readmission due to cardiovascular events.(c)Seattle Angina Questionnaire (SAQ): The degree of pain in angina pectoris, the frequency and duration of acute paroxysmal angina pectoris, etc.(d)Routine admission examination: Carotid artery color Doppler ultrasound, cardiac color Doppler ultrasound, electrocardiogram, transcranial color Doppler ultrasound, chest radiograph, and other imaging examinations; Clinical biochemical tests such as troponin, brain natriuretic peptide, emergency 7 items, myocardial enzyme, D-dimer, coagulation four items, hematuria and stool routine, etc.3.Adverse events:(a)Produce toxic reactions (such as severe gastrointestinal reactions, gingival bleeding, etc).(b)Anaphylactic shock.(c)Liver and kidney function damage caused by TCM.

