#### Diagnostic criteria of western medicine

2.2.1

Diagnostic criteria for CHD angina pectoris: According to the guidelines for the diagnosis of CHD angina pectoris formulated by the American Heart Association and the Heart Association (ACC/AHA) in the Guidelines for the Treatment of Chronic Stable Angina Pectoris (2007) and the Guidelines for the Management of Patients with Unstable Angina Pectoris and Non-ST-Elevation Myocardial Infarction (2011), and referring to the Guidelines for the Diagnosis and Treatment of Chronic Stable Angina Pectoris in China in 2007, and the Guidelines for the Diagnosis and Treatment of Unstable Angina Pectoris and Non-ST-Elevation Myocardial Infarction in China in 2007, diagnostic criteria are formulated by Chinese Society of Cardiology, Chinese Journal of Cardiology. And the Chinese Medicine Research Association of China and Western Medicine combined with the Cardiovascular Disease Prevention and Rehabilitation Committee established the Standard for the Consensus of Integrative Medicine for Integrative Medicine for the Treatment of Coronary Heart Disease (2019).

Diagnosis can be made by meeting any one or more of the following:

1.The definite history of old myocardial infarction.2.Coronary angiography or computed tomography angiography examination showed that the diameter of at least 1 main branch of coronary artery was ≥50%.3.Patients with ST-segment depression or T-wave inversion after coronary revascularization (percutaneous transluminal coronary intervention [PCI] or coronary artery bypass grafting [CABG]).

The diagnosis of unstable angina pectoris of CHD refers to the Guidelines for Diagnosis and Treatment of Unstable Angina Pectoris and Non-ST-Segment Elevation Myocardial Infarction issued by Chinese Society of Cardiology and Chinese Journal of Cardiology in 2007, including the following subtypes:

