#### Inclusion criteria

2.2.3

The inclusion criteria were as follows:

1.Voluntary participation, understanding, and signing of informed consent form.2.The age ranged from 35 to 75 years old and gender is not limited.3.For patients with angina pectoris of CHD in the inpatient department or outpatient department of cardiology, the diagnosis of angina pectoris conforms to the relevant guidelines issued by ACC/AHA, Chinese Society of Cardiology and Chinese Journal of Cardiology.4.For patients who meet the standard of drug therapy, the exposed group is treated with Chinese patent medicine combined with conventional western medicine, while the nonexposed group is treated with conventional western medicine alone.

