### Sample size calculation

2.3

The sample size calculation formula is shown in Figure 2. The expected incidence rates of exposed group and nonexposed group were obtained through literature review,^[18,19]^
*P*
_1_ = 0.072, *P*
_0_ = 0.059, *q* = 1 − *p*, *Z*
_*α*_ and *Z*
_*β*_ were the areas under the standard normal distribution, and the table was found to obtain *Z*
_*α*_ = 2.58, *Z*
_*β*_ = 1.64. Substituting the above values into the formula can be obtained, and the sample size of each group is about 5677 cases. Control the rate of loss of follow-up within 10%, mainly to ensure a certain professional representation. There were about 6200 cases in each group, and the total sample size of this study was about 12,400.

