### Regulations on combined use of drugs

2.6

Patients with CHD angina pectoris can be treated with the original scheme before admission during the study period, and the admission period is 2 weeks, so that the patient's condition is stable and meets the admission criteria.

During the study period, for patients with hypertension, diabetes, hyperlipidemia, and other diseases, the antihypertensive, hypoglycemic, and lipid-lowering treatment schemes before admission can be maintained. The name, dosage, and usage of the drugs are recorded in detail in the study medical records. It is forbidden to adjust the dosage and usage of β-receptor blockers, calcium ion antagonists, and other drugs that affect the curative effect of CHD angina pectoris.

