### Follow-up time point

2.7

Patients need to be hospitalized for 2 weeks as the introduction period and whether to enter the group is determined according to the treatment and medication conditions of the patients. The follow-up time points were 0th, 4th, 12th, 24th, and 48th weeks. The main curative effect, secondary curative effect, and concomitant medication changes of patients were observed.

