## Discussion

3

The results of cohort study belong to Class II evidence-based medicine and have advantages such as long-term, large sample, and so on. In the prospective cohort study, we can directly obtain the 1st-hand data on exposure and outcome, so the bias of the data is small. On the basis of the National Basic Research Program of China (973 projects), this study has carried out a rigorous and meticulous design of this plan and has the following advantages:

1.Fully collect important clinical-related results and the main indicators, secondary indicators and adverse event reports included in the test.2.Strict concomitant medication regulations: As patients with CHD are often complicated with hypertension, hyperlipidemia, and other diseases, or undergo PCI surgery, they need to take antihypertensive, antiplatelet agglutination, and other drugs for a long period of time. This study has strict regulations on concomitant medication, reflecting the rigor of the design.3.Accurate methodology design to reduce the risk of bias: Before statistical analysis of clinical test data, statistical analysts shall formulate statistical analysis plans, specify detailed statistical analysis steps, and carefully check, clean up and confirm clinical test data.4.Strict quality control in clinical research: Due to different clinical units, to prevent the differences in the process of collecting samples, the research group dispatched uniformly trained supervision and inspection personnel to carry out off-site and on-site supervision and inspection work on clinical units to ensure the strictness of the patients enrolled. The filling of clinical scales is also carried out after training, and professional personnel supervise and verify the data on site. The later research group uniformly conducts 2 rounds of verification on the data to ensure the accuracy of the original data.5.Unified sample collection and testing: Collected blood and urine samples are collected, transported, processed, and stored in a unified way. Biochemical indexes, liquid chips, and expression spectrum chips are all detected by professional companies to ensure the unity of the detection process.

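### The main event counts PCI and CABG without separating procedures already scheduled or staged at week 0 from those decided afterwards

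*Protocol article*

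**What the plan says.** Section 2.8.4 of the protocol article, item 1, gives the primary outcome: "Main events: The incidence of cardiovascular events includes acute myocardial infarction, PCI or CABG". It carries no qualifier such as unplanned or decided after entry.

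The population and timing are set elsewhere:

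- Section 2.2.3 takes patients from both settings: "For patients with angina pectoris of CHD in the inpatient department or outpatient department of cardiology".
- Section 2.7 says "Patients need to be hospitalized for 2 weeks as the introduction period", after which group entry is decided. Section 2.6 gives the purpose of that period: "the admission period is 2 weeks, so that the patient's condition is stable and meets the admission criteria".
- Section 2.2.1 lists as one diagnostic route "Patients with ST-segment depression or T-wave inversion after coronary revascularization". Other routes are old infarction and angiographic disease of at least 50%, and several unstable angina subtypes are described.
- The Discussion accepts PCI as part of usual care, saying that patients have other diseases "or undergo PCI surgery, they need to take antihypertensive, antiplatelet agglutination, and other drugs for a long period of time".
- Section 2.7 sets the visits: "The follow-up time points were 0th, 4th, 12th, 24th, and 48th weeks".

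None of the nine exclusion criteria in section 2.2.4 concerns a scheduled procedure. The week-0 list in section 2.8.6 has no item for one. The regression in section 2.11.2 names age, sex and treatment, and leaves the remaining factors open.

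**The concern.** A PCI or CABG booked before week 0 belongs to care already chosen and cannot be a result of adding Chinese patent medicine. Followed as written, section 2.8.4 would let a site score a second-stage PCI booked before entry and carried out in week 3 as a main event.

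Two consequences are possible. If pending procedures are equally common in both groups, they add events that treatment cannot affect and pull the risk ratio towards 1. If they are not, the difference goes directly into the primary result. Inequality is plausible because treatment is chosen, not randomised, and the revascularisation plan may be known when it is chosen. The bias could run either way, and a larger sample would not remove it. A status that is not recorded at week 0 cannot be adjusted for later.

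**Working it through.** **Inputs.** From section 2.3: rates 0.072 and 0.059, and 5677 per group. From section 2.11.2: two-sided alpha 0.05. The frequency of planned procedures is given nowhere, so every such figure below is my assumption. I use the larger rate over the smaller, so nothing here depends on which group carries the higher rate.

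**The plan's own figures.**

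- Risk ratio: 0.072/0.059 = 1.22. Difference: 1.3 points.
- n = [Zα√(2p̄(1−p̄)) + Zβ√(p1(1−p1)+p0(1−p0))]²/(p1−p0)², with p̄ = 0.0655.
- With the stated Z values 2.58 and 1.64, n = 12,897 per group, so the stated 5677 is not reproduced.
- With 1.96 and 0.84, n = 5678. The stated figure therefore matches two-sided alpha 0.05 and 80% power. That discrepancy is a separate matter. Below I take 5677 per group and alpha 0.05.

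**Power formula.** Power = Φ{[|p1−p0| − 1.96√(2p̄(1−p̄)/n)] / √([p1(1−p1)+p0(1−p0)]/n)}. For 0.072 against 0.059 and n = 5677: (0.0130 − 0.0091)/0.00464 = 0.84, power 80%.

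**A. Balanced planned procedures, added on top of the stated rates.**

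| Added to both groups | Rates | Risk ratio | Power |
|---|---|---|---|
| 0 points | 7.2% v 5.9% | 1.22 | 80% |
| 1 point | 8.2% v 6.9% | 1.19 | 75% |
| 2 points | 9.2% v 7.9% | 1.16 | 70% |
| 3 points | 10.2% v 8.9% | 1.15 | 65% |

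**B. Balanced planned procedures, already inside the stated rate.** Keep the higher rate at 7.2%, let a share s of it be planned, and apply the stated ratio 0.059/0.072 = 0.819 only to the rest. The lower rate is then 0.072s + 0.072(1−s) × 0.819.

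| s | Rates | Risk ratio | Power |
|---|---|---|---|
| 10% | 7.20% v 6.03% | 1.19 | 71% |
| 20% | 7.20% v 6.16% | 1.17 | 60% |
| 30% | 7.20% v 6.29% | 1.14 | 49% |

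**C. Unequal planned procedures, no drug effect.** Take 5.9% in both groups for all other events.

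- Planned 3.0% v 1.7%: totals 8.9% v 7.6%, risk ratio 1.17, about a 71% chance of P < 0.05.
- Planned 2.0% v 1.5%: totals 7.9% v 7.4%, risk ratio 1.07, about a 17% chance of P < 0.05.

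These show how sensitive the result is to imbalance. They do not show that such an imbalance is likely.

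**The case against.** The strongest reply is that this rests on silence. No sentence says that planned procedures count, and the item's opening words could be read as meaning new events. The text is a condensed article: event definitions may sit in a full protocol, CRF or analysis plan that is not shown, and the data-collection table is not visible. This limits how firmly the point can be put. It does not remove it, because the article does define its primary event and that definition draws no line. Whether pending procedures are recorded must also be settled at data collection and cannot be left to the analysis.

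A reader might go further and infer that part of the primary outcome is in fact decided before week 0 in a cohort recruited during admission. The documents do not support that:

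- Outpatients are also eligible under section 2.2.3, which needs reconciling with the 2-week hospital period in section 2.7.
- Entry follows a stabilisation period, so many index-stay procedures may fall before week 0. Staged or deferred ones would remain, but no passage mentions staging. The post-revascularisation diagnostic route describes ECG changes after a completed procedure, not a pending one.
- No frequency of planned procedures is given, so the effect may be nil.

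It is also fair to say that adding points on top of the stated rates could double count. "The expected incidence rates of exposed group and nonexposed group were obtained through literature review", and section 2.3 does not give the event definition behind those rates. Scenario B covers that case. Finally, unequal planning is a form of confounding, and the regression in section 2.11.2 could adjust for planning status, but only if it is recorded.

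**Conclusion.** The point holds as a weakness in the endpoint definition. As written, the main event does not distinguish procedures pending at week 0 from later ones, and the listed exclusions and week-0 data neither remove nor capture them. The likely effect is dilution if they are balanced, and bias of unknown direction if they are not.

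The size cannot be fixed from the documents. On the assumption of 1 to 3 points in both groups, the risk ratio moves from 1.22 to between 1.19 and 1.15, and power at 5677 per group falls from 80% to between 75% and 65%. If there are no planned procedures, nothing changes. Imbalance is the greater risk because the planned difference is only 1.3 points. The point deserves correction, but it does not show that the primary result would be invalid.

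**What to change.** 1. At week 0, record on the CRF whether a PCI or CABG is already scheduled or staged.
2. Define the main event as acute myocardial infarction, or a PCI or CABG not flagged as planned at week 0. Do not add a condition on the reason for the procedure: follow-up is partly by telephone and WeChat, no blinding is described, and such a condition would bring in a judgement that the flag avoids.
3. Report flagged procedures separately by group, and keep following those patients for later main events.
4. Keep any PCI or CABG as a sensitivity analysis.

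The cost is one CRF item, one sentence in section 2.8.4 and somewhat fewer events. Fewer events need not mean less power. In scenario B with s = 20%, removing the planned procedures gives 0.8 × 7.2% = 5.76% against 0.8 × 5.9% = 4.72%. The difference stays at 1.04 points, and power is Φ[(0.0104 − 1.96 × 0.00418)/0.00418], about 70%, compared with 60% when they are counted. A planned procedure can alter later risk, so the flag should also be available as a covariate.

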## Introduction

1

Coronary heart disease (CHD) is a heart disease caused by myocardial ischemia and hypoxia due to coronary atherosclerosis. Angina pectoris is closely related to coronary artery insufficiency and is common in clinical practice.^[1,2,3]^ Patients with CHD angina pectoris are in critical condition, which can cause sudden death, myocardial infarction, and other adverse events, and bring serious burden to families and society. Timely treatment should be given to improve the condition.^[2,3,4,5]^ Clinical attention has long been paid to the treatment of CHD angina pectoris. Western medicine for angina pectoris mainly uses β-receptor blocker, calcium channel blocker, angiotensin converting enzyme inhibitor, angiotensin II receptor antagonist, etc.^[6]^ It has good clinical effect, but the demand for angina symptom control is still unsatisfied.^[7]^

As a unique medical resource in China, traditional Chinese medicine (TCM) plays an important role in disease treatment and health services. Chinese patent medicine is made of Chinese herbal medicines as raw materials and processed into various dosage forms of Chinese traditional medicine products, including pills, powders, granules, pastes, capsules, Chinese traditional medicine injections, aerosols, etc. Its advantages are ready availability, adaptability to urgent need, convenient storage, easy carrying, and saving decocting process, etc, and eliminating peculiar smell and adverse stimulation when taking TCM decoction.^[8,9,10]^ According to statistics, the number of Chinese patent medicines in the 2012 edition of the basic medicine catalog has increased to 203, accounting for 39%, of which 23 are Chinese patent medicines for the treatment of cardiovascular diseases.^[11]^ Eight kinds of commonly used cardiovascular Chinese patent medicines and 28 kinds of antiangina Chinese patent medicines are included in New Pharmacology.^[12]^ In recent years, many studies have shown that Chinese patent medicine has achieved certain curative effect in the dialectical treatment of angina pectoris, which has the advantages of good effect and few adverse reactions.^[13,14,15,16,17]^ However, Chinese patent medicine is difficult to match western medicine with large-scale clinical trials in treatment, health education, and publicity. Therefore, a research method with higher evidence value-clinical cohort study is needed to conduct evidence-based research on it.

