### Adverse reactions

2.5

In this study, the adverse reactions of drugs (Chinese patent medicine and conventional western medicine) studied are detailed in the drug instructions.

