#### Information collection at different time points

2.8.6

1.0th week: Collect demographic data, TCM syndromes of CHD angina pectoris, western medicine classification of CHD angina pectoris, SAQ in main curative effect and secondary curative effect, routine admission examination, genomics, proteomics, metabolomics, intestinal flora, and tongue coating flora.2.4th week: SAQ, routine admission examination, adverse events, genomics, proteomics, metabolomics, intestinal flora, and tongue coating flora were tested for primary events and secondary events.3.12th week: SAQ, routine admission examination, adverse events, genomics, proteomics, metabolomics, intestinal flora, and tongue coating flora were tested in the primary events and secondary events.4.24th week: Detect the main curative effect, death in secondary curative effect, readmission due to cardiovascular events and adverse events.5.48th week: Check the main curative effect, death in secondary curative effect, readmission due to cardiovascular events and adverse events (Table 1).

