#### Safety analysis

2.11.3

The safety analysis of each group of cases is mainly based on descriptive statistics, including the incidence rate of adverse events and abnormal changes in the specific description of adverse events and their relationship with drug administration.

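### The adverse event list in section 2.8.4 is skewed to severe reactions and has no general category, so milder reactions may be missed or recorded inconsistently

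*Protocol article*

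**What the plan says.** Section 2.8.4 item 3 of the protocol article sets out adverse events as three entries. The first two are "Produce toxic reactions (such as severe gastrointestinal reactions, gingival bleeding, etc).(b)Anaphylactic shock". The third is "Liver and kidney function damage caused by TCM". No grading scale and no general entry accompany the list.

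Four other places touch on the subject:

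- Section 2.5 says that "the adverse reactions of drugs (Chinese patent medicine and conventional western medicine) studied are detailed in the drug instructions".
- Section 2.8.6 schedules adverse events at weeks 4, 12, 24 and 48. The last entry reads "5.48th week: Check the main curative effect, death in secondary curative effect, readmission due to cardiovascular events and adverse events".
- Section 2.11.3 plans a largely descriptive safety summary for each group, "including the incidence rate of adverse events and abnormal changes in the specific description of adverse events and their relationship with drug administration".
- The Introduction says of Chinese patent medicine, on the basis of earlier studies, "which has the advantages of good effect and few adverse reactions".

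**The concern.** The entries describe mainly the serious end of what a drug can do. A mild or moderate gastrointestinal reaction does not match the example given. A rash or urticaria does not match the only allergic entry, so it is recorded only if a centre decides to call it a toxic reaction. Dizziness has no obvious place.

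The exposed group takes an added medicine on top of conventional treatment, so an excess of common, milder reactions is one of the things a safety comparison should be able to show. If such reactions go unrecorded, incidence is understated, and a low figure could be taken as support for the favourable safety profile described in the Introduction. The loss would be permanent, because no analysis plan can recover events that were never written down.

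**Working it through.** The article gives no adverse event rate, no severity breakdown and no safety sample size, so there is no stated figure to reproduce. The check is a comparison of texts, plus the little arithmetic they allow.

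**1. What each entry of section 2.8.4 item 3 admits**

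| Entry | Severity limit in the text | Open or closed |
|---|---|---|
| (a) Toxic reactions | *Severe* attached to the gastrointestinal example; none on gingival bleeding | Open: examples only |
| (b) Anaphylactic shock | Extreme by its nature | Closed |
| (c) Liver and kidney damage | None, but limited to damage caused by TCM | Closed |

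The list leans to the severe end without being wholly confined to it.

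**2. Whether another section widens the list**

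- Section 2.5 says where known reactions are described. It sets no severity limit, but it does not say that label-listed reactions are recorded as study events.
- Section 2.8.6 gives the timing of collection, not the content.
- Section 2.11.3 reports incidence and relationship to drug administration without redefining the term, so it depends on section 2.8.4.

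None of these excludes milder reactions, and none brings them in.

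**3. Room for inconsistency**

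Section 2.9 allows follow-up by interview, telephone, WeChat or the outpatient system, and section 2.11.4 names 5 centres. With contacts of that kind, the printed list is likely to shape what is asked and noted. One centre may place a mild reaction under (a) and another may not.

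**4. What can be said about size**

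Let R1 and R0 be the true proportions of exposed and nonexposed patients with any adverse event, and s1 and s0 the shares of those patients whose event is recorded.

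- Reported rate in each group: s × R.
- If s1 = s0 = s, the reported risk difference is s × (R1 − R0). It shrinks with s, while the risk ratio is unchanged.
- If s1 ≠ s0, the reported risk ratio is (s1/s0) × (R1/R0), so the ratio is distorted as well.

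The article gives none of these quantities, so the understatement has a direction but no computable amount.

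**5. What a low count would and would not show**

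Suppose, as an illustration only, that no case of anaphylactic shock is seen in the exposed group. The one-sided 95% upper bound is 1 − 0.05^(1/n).

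- n = 6200 (enrolment target per group): 1 − 0.05^(1/6200) = 0.00048.
- n = 6200 × 0.9 = 5580 (after the 10% loss allowed in section 2.3): 1 − 0.05^(1/5580) = 0.00054.

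Both are about 0.05%. That is a tight bound on one extreme event, and it carries no information about common reactions that were not collected.

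**The case against.** A reader might infer something stronger: that mild and moderate reactions are not counted at all, and that the safety result is low by construction. The documents do not support that.

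- Entry (a) is illustrative and open-ended, and the word *severe* qualifies only its gastrointestinal example.
- Gingival bleeding and entry (c) have no severity threshold.
- Sections 2.5 and 2.11.3 set no severity limit, and no section says that milder reactions are left unrecorded.
- Any fold-size for the undercount would rest entirely on an assumed share of mild events.
- The sentence on few adverse reactions summarises earlier work. The safety analysis is mainly descriptive, and no safety hypothesis is tested that the list would appear to confirm.

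All of this stands, and it limits the point to ambiguity and a likely, unquantified understatement.

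It can also be said that grading, seriousness and case report form fields normally sit in the full protocol, which a journal article condenses. That is fair as far as it goes, and their absence alone would be no finding. But the article does not leave the definition to another document. It prints one, and the printed one is skewed. The Discussion also counts full collection of adverse event reports among the design's strengths, which this list does not secure.

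**Conclusion.** The point holds as one of poor definition. The only printed list of adverse events is weighted to severe reactions, names anaphylactic shock as its sole allergic entry and has no general category. Milder reactions are neither excluded nor clearly included. Centres following the list may omit them or record them unevenly, so the incidence under section 2.11.3 is liable to be understated, and its meaning may vary by centre.

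The amount cannot be computed from the documents. The conclusion assumes that the printed list guides what is recorded; if the full protocol or the case report form already asks for events of every grade, only the wording of section 2.8.4 needs correcting. The change should be made, but the documents do not show that the safety comparison is bound to fail.

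Entry (c) adds a related reason for a common definition. Because it requires the damage to be caused by TCM, liver or kidney damage in a nonexposed patient cannot qualify, and the two groups are not counted alike.

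**What to change.** In section 2.8.4 item 3, define an adverse event as any untoward medical occurrence during follow-up, of any severity, applied identically in both groups. Record severity, seriousness, action taken and relationship to drug as separate case report form fields, so that causality is judged after an event is recorded and is not a condition for recording it. Keep the reactions now listed as events of special interest, with liver and kidney damage recorded in both groups whatever its suspected cause.

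In section 2.11.3, report incidence by group for all events, serious events and events leading to discontinuation, each with the risk difference and its 95% confidence interval.

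The cost is protocol wording, extra form fields and somewhat more event recording at the contacts already planned for weeks 4, 12, 24 and 48. No new visit or test is needed.

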## Method

2

A prospective cohort study was conducted among patients with CHD angina pectoris who were treated with oral Chinese patent medicine and conventional western medicine. The patients were divided into exposed group and nonexposed group according to whether or not the patients with CHD angina pectoris were treated with Chinese patent medicine. The exposed group was treated with TCM combined with conventional western medicine, while the nonexposed group was treated with conventional western medicine alone. Patients need to be hospitalized for 2 weeks as the introduction period and whether to enter the group is determined according to the treatment and medication conditions of the patients. The follow-up time points were 0th, 4th, 12th, 24th, and 48th weeks. The main events, secondary events and adverse events were used as the evaluation criteria for clinical efficacy of CHD angina pectoris. In the experimental study, we will use strict indicators to detect standard operation procedure for multigroup and bacteria detection. It is hoped that the research method with higher evidential value will be adopted to compare the short-term, medium-term, and long-term effects of Chinese patent medicine combined with conventional western medicine and conventional western medicine alone in the treatment of CHD angina pectoris, so as to tap the clinical efficacy advantages of TCM and provide reliable data support for its clinical application. The technical route is shown in Figure 1.

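### Liver and kidney damage counts as an adverse event only if Chinese medicine caused it, so this item and any pooled rate containing it cannot be compared between groups

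*Protocol article*

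**What the plan says.** The protocol article, section 2.8.4, item 3, names three kinds of adverse event:

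- (a) "Produce toxic reactions (such as severe gastrointestinal reactions, gingival bleeding, etc", an open-ended list;
- (b) "Anaphylactic shock";
- (c) "Liver and kidney function damage caused by TCM".

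Section 2 (Method) defines the groups: "The exposed group was treated with TCM combined with conventional western medicine", while "the nonexposed group was treated with conventional western medicine alone". The same section names adverse events, with main and secondary events, among the evaluation criteria.

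Section 2.11.3 sets the analysis: "The safety analysis of each group of cases is mainly based on descriptive statistics, including the incidence rate of adverse events". It goes on to events and "their relationship with drug administration". Section 2.5 refers to adverse reactions of both Chinese patent medicine and western medicine. Section 2.8.6 collects adverse events at weeks 4, 12, 24 and 48 without distinguishing the groups.

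**The concern.** Item (c) puts a causal judgement about one group's treatment into the definition of the event. A nonexposed patient whose liver or kidney function deteriorates, for instance on a statin or an ACE inhibitor (both listed in section 2.4.2), does not meet it. An exposed patient takes the same western drugs as well, and meets it only if the damage is put down to Chinese medicine.

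Incidence by group then sets a rate of attributed damage in one group beside a zero fixed in advance in the other. That can suggest harm where there is none, or understate harm that exists. It can never show less organ damage in the exposed group, although the Introduction gives few adverse reactions as an advantage of Chinese patent medicine.

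**Working it through.** The documents give no adverse-event rate, margin or power for safety, so there is no stated figure to reproduce. The check is mainly a reading of the text, with an illustration of size.

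**Text.**

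| Place | Tied to one treatment? |
|---|---|
| 2.8.4, 3(a) toxic reactions | No |
| 2.8.4, 3(b) anaphylactic shock | No |
| 2.8.4, 3(c) liver and kidney damage | Yes, Chinese medicine only |
| 2.5 adverse reactions | No, both drug classes |
| 2.11.3 safety analysis | No; incidence for each group, relationship with the drug described as well |

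Only 3(c) carries the restriction. It fits neither section 2.5, which covers both drug classes, nor section 2.11.3, where the relationship with the drug is a descriptor of an event and not a condition for being one.

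**General form.** Let r1 and r0 be the true all-cause rates of liver or kidney damage in the exposed and nonexposed groups, and f the share of exposed cases attributed to Chinese medicine.

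- Recorded under 3(c): f × r1 (exposed) and 0 (nonexposed).
- True difference: r1 − r0. Recorded difference: f × r1.
- Error = f × r1 − (r1 − r0) = r0 − (1 − f) × r1.

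The error can take either sign. The recorded difference is never below zero, so r1 < r0 cannot appear.

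**Illustration, equal true rates.** N = 5677 per group (section 2.3, before allowance for loss). The rates r and shares f are assumptions. Expected all-cause count per group = r × N; recorded exposed count = r × f × N; recorded nonexposed count = 0.

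| r | All-cause count, each group | Exposed, f = 25% | Exposed, f = 50% | Exposed, f = 100% | Nonexposed |
|---|---|---|---|---|---|
| 0.1% | 5.7 | 1.4 | 2.8 | 5.7 | 0 |
| 0.5% | 28.4 | 7.1 | 14.2 | 28.4 | 0 |
| 1% | 56.8 | 14.2 | 28.4 | 56.8 | 0 |
| 2% | 113.5 | 28.4 | 56.8 | 113.5 | 0 |

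As a gauge only, since no such test is planned, a pooled two-proportion statistic is z = r f / √(2 p̄ (1 − p̄) / N), with p̄ = r f / 2. At r = 1% and f = 100% it is 0.01 / √(2 × 0.005 × 0.995 / 5677) = 7.55. Over the table it runs from 1.19 to 10.71, although the true rates are equal throughout.

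**Illustration, true excess.** Assume r1 = 2% and r0 = 1%. The true counts are 113.5 and 56.8, an excess of 1 percentage point. With f = 25% the rule records 28.4 and 0, an excess of 0.25 × 2% = 0.5 points. With f = 100% it records 113.5 and 0, an excess of 2 points.

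**The case against.** Several points stand against a stronger reading.

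- A reader might infer that the whole safety comparison is invalid. The text does not support that: items (a) and (b) are worded alike for both groups and stay comparable.
- The safety analysis is mainly descriptive, with no named between-group test, margin or hypothesis. The distortion is therefore one of reported rates, not of a formal test. Since adverse events are among the evaluation criteria, readers will still set the two rates side by side.
- Adverse events are collected without restriction by group, relatedness is already to be described, and item (a) is open-ended enough to admit organ toxicity of western drugs. So the documents do not prove that nonexposed injuries will go unrecorded. But listing (c) separately points away from placing organ damage under (a). If some sites did so, the same injury would be classified differently by group.
- A reader might infer that an excess of organ damage cannot be measured at all. That is not established. Section 2.8.6 schedules routine examinations at weeks 0, 4 and 12, and section 2.8.4 lists biochemical and urine tests among them. Whether liver and kidney function tests are included is not stated.
- With perfect attribution, f would equal (r1 − r0) / r1 whenever r1 is at least r0, and the recorded difference would be correct. This holds in principle, but it makes the result depend on separating two drug classes in patients who take both. Who makes that judgement, and whether they know the exposure, is not stated; a condensed article may leave that to the full protocol, so no fault is claimed there.

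**Conclusion.** Item 3(c) is wrong as written for a two-group cohort. Followed literally, it gives a structural zero in the nonexposed group and leaves out damage from other causes in the exposed group. The incidence of this item, and of any pooled adverse-event rate containing it, is not comparable between groups. It is also inconsistent with sections 2.5 and 2.11.3.

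The structural zero needs no assumption beyond the literal wording and the group definitions. The counts do: the rates of 0.1% to 2% and the attribution shares are illustrative and have no source in the documents. They show only that the distortion can range from a case or two to more than a hundred.

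This should be fixed, ideally before data collection, because an event that is never recorded cannot be recovered in the analysis. It is not critical to the trial's main conclusion: the primary outcome and its analysis are untouched.

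**What to change.** In section 2.8.4, item 3(c), delete the final three words of "Liver and kidney function damage caused by TCM", so that liver or kidney function damage is defined identically in both groups regardless of cause. On the case report form, record relatedness to Chinese patent medicine and to western medicine as a separate field. In section 2.11.3, report all-cause incidence by group first, with related events as a secondary table.

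The cost is a change of wording in the protocol and case report form, and slightly more adverse-event recording in the nonexposed group. The change concerns the definition, not the visit schedule, so it requires no additional laboratory visits.
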